#### 2.8.8. Hormone Level Measurements

Hormonal changes related to the glycemic control and satiety level of the participants will be measured in this study to understand the underlying pathway of meal replacement effects on obese and overweight T2DM patients. The hormones related to glycemic control that will be studied are adiponectin and leptin. The hormones related to satiety that will be studied are ghrelin, obestatin, and peptide YY. Adiponectin, leptin, ghrelin, obestatin, and peptide YY levels will be analysed through Enzyme-Linked Immunosorbent Assay (ELISA) commercial kits. The procedures for hormone analysing will be based on each kit protocol.

#### 2.8.9. Quality of Life

##### Audit of Dependent Diabetes Quality of Life (ADDQOL-19)

A validated Malay language translated ADDQOL-19 questionnaire will be used in this study to determine the quality of life (QoL) [32]. Good validity and reliability have been reported for ADDQOL-19 [32]. ADDQOL is comprised of 21 items with 19 items related to specific life domains and two overview items measuring general aspects [33]. The participants will be assisted by the researcher in understanding and completing the questionnaire.

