### 2.5. Randomisation

Following the baseline measurement, participants will be randomised into the MR group and control group at a 1:1 ratio. A third-party statistician will carry out the randomisation using the Winpepi computer program with minimisation method [19]. Gender (men, women), HbA1c (≤8.5% or >8.5%), and BMI (≤25 or >25) at the time of baseline measurement will be balanced in each group. Treatment allocation will not be blinded to both researchers and participants due to the nature of the intervention. The participants will be informed about which group they should accordingly be in before the intervention process starts.

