#### 2.8.10. Cost-Effectiveness

Quality-adjusted life years (QALY) will be the main outcome parameter for the evaluation of cost-effectiveness from a societal perspective. EuroQol five-dimension Inventory (EQ-5D-5L) will be utilised in this study to calculate QALY. It is the most used instrument worldwide in economic evaluations that measure health benefits in terms of QALY [43]. English and Malay versions of EQ-5D-5L, which have been validated for use in the Malaysian population, will be utilised in this study [44,45].

EQ-5D-5L is a self-report questionnaire that assesses five life domains, including mobility, self-care, usual activities, pain/discomfort, and anxiety/depression [43]. There is also an EQ-VAS section to measure respondents’ perception of their overall current health on a vertical visual analogue scale with ‘100′ corresponding to ‘The best health you can imagine’ and ‘0′ representing ‘The worst health you can imagine’.

Scores on the five dimensions will be totalled up and converted into utility weights for computing QALY using the EQ-5D algorithm. Analysis will be conducted to estimate the direct and indirect costs for the intervention group and the control group for routine diabetes care. Intervention costs will then be estimated by using a bottom-up micro-costing analysis that will include meal replacement cost and operational costs such as dietician’s salary. The cost for control group or routine diabetes care will be estimated from a questionnaire on participant’s health care utilisation (general practitioner, dietician, physiotherapist, consultations at outpatient clinic, and hospitalisation) and use of medication.

The cost per QALY gained will be computed, and incremental cost-effectiveness ratios (ICER) will be calculated as the difference in costs divided by the difference in QALYs between the intervention and the control group using a bootstrap analysis. A cost-effectiveness plane can be plotted to indicate which intervention is more effective or expensive than the other.

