## 4. Discussion

The global epidemic of obesity and associated T2DM direly needs a greater emphasis on effective lifestyle intervention programs for patients. Meal replacement is often included as a part of the lifestyle intervention program as it is effective as an initial phase for diabetic patients to lose weight in a therapeutic program [46]. Previous trials utilising meal replacements on obese or T2DM patients have demonstrated significant improvements in HbA1c, weight, lipid profile, insulin sensitivity, and cardiovascular risk factors [47,48,49,50,51].

This prospective, randomised, controlled open-label trial will focus on evaluating the effectiveness of a diabetes-specific meal replacement formulation on the weight loss and glycemic control of obese and overweight T2DM patients. To date, this is the first trial of its kind to test the efficacy of this low glycemic indexed meal replacement formulation containing cinnamon extract (*Cinnulin MS*) on overweight or obese T2DM patients. There is also a lack of studies on short-term meal replacement intervention in a sufficiently powered and well-designed clinical trial in Malaysia. We hypothesised that the meal replacement intervention would be effective in maintaining weight loss, improving glycaemic control parameters, and improving the quality of life of the participants.

Apart from anthropometry and biochemical analysis, a cost-effectiveness analysis of the meal replacement intervention will also be conducted, in comparison with the standard care in public. It is anticipated that this meal replacement intervention in T2DM management would be more cost-effective, as simulated in the other study (Stephen 2010).

Meal replacements have been proven to improve patients’ weight and glycaemic control. However, due to the lack of further intervention following the completion of the initial intervention, it has also been shown to be less effective in maintaining glycaemic control in some meal replacement studies. This is shown in a study by Ash et al., in which the HbA1c levels of the participants who received a 12-week diet intervention with meal replacement returned to baseline levels after their 18th month follow-up [16]. Similar results of weight and HbA1c levels rebounding have been reported in other studies [52,53,54].

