One of these methods is to utilise telecommunication software to conduct the diet education online for digitally literate participants. Based on a survey by the American Society of Clinical Oncology on clinical trial participants, nearly all of their respondents (90.3%) indicated telehealth as a potential alternative for conducting clinical trials during the pandemic [60]. Step-by step instructions will be provided to the participants on utilising the online meeting software for conducting diet education. Patient reviews of compliance to meal replacement and adverse events can also be monitored through telecommunications methods such as email, phone, or messaging applications. A study by Aravindhan et al. [61] has reported that virtual interviews for older research participants, because of lockdown measures, are feasible in the current pandemic situation to minimise physical sessions.

Home visits will also be carried out for patients who are unwilling to attend the site for intervention. The phlebotomist and a researcher will visit the patient’s house for blood taking, assisting in the completion of questionnaires and providing instructions on the trial. Strict standard operating procedures will be adhered to in order to ensure the safety of the trial participants and the researchers from COVID-19. This is as suggested by the FDA, who states that consideration should be given for alternative locations for visitations if a patient is not able to go to the investigational site [55]. The investigational product, which is the meal replacement powder, will also be delivered to the participants’ homes [62].

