### 4.1. Limitation

The major limitation of this trial is that it is a single-centred study. Hence, the generalisability of the study might be limited to the Malaysian T2DM population who visit the public health sector to seek treatment. Meal replacement products are also given to the participants without any charge. This might also impact the generalisability of the study, as dropout rates for less motivated patients in real-world settings in such intervention programs are likely to be higher. To reduce this limitation from the generalisability perspective, we have used randomisation techniques during sampling to maximise the representation of our target population.

Due to the nature of the study, the treatment allocation will not be blinded to both participants and the researchers. However, to minimise selection bias, randomisation into groups and statistical analysis will be carried out by a third-party statistician.

The taste and texture of the meal replacement we are studying might also affect the compliance of the participants, as there are reports from testers who dislike the cinnamon taste of the liquid meal replacement. We will inform our study participants beforehand to get them to gradually adapt to the taste.

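### A researcher who knows the allocation helps participants understand and complete the ADDQOL-19, which leaves an avoidable route for arm-specific bias in the post-randomisation quality-of-life answers

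*Protocol article*

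**What the plan says.** - **How the ADDQOL-19 is completed** (protocol article, 2.8.9, ADDQOL-19): "The participants will be assisted by the researcher in understanding and completing the questionnaire". The help covers meaning as well as filling in the form, and it is stated for participants in general.
- **Blinding** (2.5): "Treatment allocation will not be blinded to both researchers and participants due to the nature of the intervention".
- **Order of events** (2.5): "Following the baseline measurement, participants will be randomised into the MR group and control group at a 1:1 ratio".
- **Home visits** (4. Discussion): for patients unwilling to attend the site, a researcher and a phlebotomist go to the home. The tasks include "assisting in the completion of questionnaires and providing instructions on the trial". No questionnaire is named or exempted.
- **EQ-5D-5L** (2.8.10): "EQ-5D-5L is a self-report questionnaire that assesses five life domains". It supplies the utilities for the QALYs.
- **Role of quality of life**: it is a secondary endpoint (1.1.2), and the hypothesis (4. Discussion) includes "improving glycaemic control parameters, and improving the quality of life of the participants".
- **Safeguard offered for the open-label design** (4.1): "randomisation into groups and statistical analysis will be carried out by a third-party statistician". Its stated aim is to limit selection bias.

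**The concern.** The reason given for not blinding is the nature of the intervention. That explains why participants know their arm. It does not explain why the person clarifying quality-of-life items must also know it, or why that person should explain items freely.

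The two arms also differ in contact with the trial team. Section 2.7 provides daily reminders and telephone follow-up about taking the product. Section 2.6.2 leaves controls without further intervention after the consultation. A helper from that team could therefore frame items differently in the two arms without intending to.

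At stake is the quality-of-life part of the hypothesis. A shift introduced by the helper would look like a treatment effect, and the protocol has no means of telling the two apart.

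**Working it through.** **1. Which answers are exposed.** Table 3 schedules the ADDQOL-19 at weeks 0, 12, 24, 36 and 48. Randomisation follows the baseline measurement, so at week 0 there is no allocation for the helper to know. The four later assessments are exposed. An unaffected baseline does not cancel the problem: section 2.9 tests the group-by-time interaction, and a shift in one arm after baseline falls on that interaction.

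**2. Which questionnaires are exposed.**
- ADDQOL-19: stated directly in 2.8.9.
- DTSQ and DDS: their own sections mention no help; exposure comes only through the home-visit text.
- EQ-5D-5L: called self-report in 2.8.10; exposure is possible only through the home-visit text. The number of home visits is not given.

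**3. Whether a stated safeguard covers it.** Randomisation and analysis by a third party act before and after the answers are given. Neither affects how the answers are obtained. The article mentions no script and no limit on the help.

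**4. Illustration of size.** The plan gives no figure for this point. Its sample size is used here only to set the arm sizes, and it reproduces: λ = N·f²·m / (1 + (m − 1)ρ) = 120 × 0.2055067² × 4 / 2.5 = 8.1087, with power 0.8063, as in Table 2. That calculation is for HbA1c, not quality of life.

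Arm sizes: 156 / 2 = 78 with no dropout; 156 × 0.70 / 2 = 54.6, taken as 55, with the 30% dropout the plan allows for.

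Assumptions not in the documents: no true effect; the helper alone shifts the mean answer in one arm, in the favourable direction, by b standard deviations averaged over the whole arm; one visit is compared by a two-sided 5% z-test.

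SE of the standardised difference = √(2/n): √(2/55) = 0.191 and √(2/78) = 0.160.

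P(significant benefit) = P(Z > 1.96 − b/SE). For b = 0.2 and n = 55: 1.96 − 0.2/0.191 = 0.91, which gives 0.181.

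| Assumed shift b | 55 per arm | 78 per arm |
|---|---|---|
| 0 | 2.5% | 2.5% |
| 0.1 SD | 7.6% | 9.1% |
| 0.2 SD | 18.1% | 23.9% |
| 0.3 SD | 34.9% | 46.6% |

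Because b is an average over the arm, the shift per helped participant must be larger if only some are helped. If half were helped, b = 0.2 would need 0.2 / 0.5 = 0.4 SD in each.

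**The case against.** **Help can be good practice.** Assistance with a 21-item form can protect completeness and understanding, and nothing says it is leading. A condensed article may also leave a neutral script to the full protocol. This stands as a reason not to forbid help. It does not remove the point, because the article states that help extends to understanding and sets no limit on it.

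**The scope is narrow.** A reader might infer that the QALYs and the cost-effectiveness result are biased. The documents do not support that: the EQ-5D-5L is described as self-report, and the only link is a pandemic contingency that names no instrument. It is a possibility at home visits, no more.

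**How often help is needed is unknown.** A reader might take the ethnic mix in Table 4, set against Malay-language instruments, as a sign that help will be frequent. Ethnicity does not measure language ability, the table describes people identified from records rather than enrolled, and randomisation should balance language need between arms.

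**The shift is assumed.** The 0.1 to 0.3 SD range has no source in the documents, and a single-visit test is not the planned mixed-design ANOVA. This stands in full: the table shows sensitivity to an assumption, not an expected error rate.

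**Quality of life is secondary and the open-label conduct is disclosed.** Also true. Participants know their own arm, and that source of bias stays whatever is done about the helper.

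**Conclusion.** The point holds in limited form. A stated procedure has an unblinded researcher help with the understanding and completion of the ADDQOL-19, and no stated safeguard acts on that step. Answers at weeks 12, 24, 36 and 48 are exposed; baseline answers are not. For the other questionnaires, exposure is possible only through the home-visit text.

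The size of any shift is unknown. The illustration shows only that a modest shift, if it occurred, would matter: 0.2 SD would take the chance of a false benefit from 2.5% to between 18% and 24% in a single-visit comparison. It would be wrong to conclude that the quality-of-life result is invalid or that such a shift is expected. The HbA1c endpoint, a laboratory measure, is untouched. The conclusion rests on reading the researcher in 2.8.9 as one of the unblinded researchers of 2.5. The change is worth making because it is cheap and removes the avoidable part of the bias.

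**What to change.** Replace the sentence in 2.8.9, and align the home-visit text in the Discussion, so that:

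1. In both arms, participants complete all questionnaires themselves at the start of each visit, before any discussion of product, compliance or results.
2. Where help is needed, it follows one fixed neutral script used identically in both arms: items read as worded, set clarifications only, and no interpretation of answers.
3. The form records whether help was given.
4. The quality-of-life analysis is repeated without assisted forms as a sensitivity analysis.

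If a script already exists in the full protocol, the sentence should refer to it. The change matters at the post-randomisation visits; using the same procedure at baseline keeps the measurements comparable.

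Cost: a reworded visit procedure, a short script and one tick box, with no extra staff and no change to sample size or intervention. The downside is a few more unanswered items and a smaller sample in the sensitivity analysis. Section 3 reports that the intervention had not started, so on that account the change could be in place before any exposed answer is collected.

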##### Diabetes Treatment Satisfaction Questionnaire (DTSQ)

The Diabetes Treatment Satisfaction Questionnaire (DTSQ) will be used to measure participants’ satisfaction with the diabetes treatment regimens that include pre- and post-intervention [37]. DTSQ has been recommended as a useful tool by the World Health Organization (WHO) and the International Diabetes Foundation (IDF) for diabetes care outcome measurements [38]. It has been widely used to measure patient satisfaction with diabetes treatments.

Two versions of DTSQ will be utilised in this study, which are DTSQ status (DTSQs) and DTSQ change (DTSQc). DTSQs contain a six-item scale assessing treatment satisfaction and two items assessing the perceived incidence of hyperglycaemia and hypoglycemia. The six-item scale ranges from 0 (never) to 6 (always).

DTSQc contains the same eight-item scale but asks patients about their satisfaction with their current treatment as compared to their previous treatment [39]. It will be used to supplement DTSQs during post-treatment to overcome its ceiling effects where respondents who scored maximum or near-maximum satisfaction may show no improvement after the intervention [40]. The assessment of DTSQ will be performed by obtaining the mean scores and comparing them during pre- and post-intervention.

##### Diabetes Distress Scale (DDS)

The Diabetes Distress Scale (DDS) is a 17-item scale used to measure diabetes-related emotional distress [41]. A translated and validated Malay language version of DDS will be used in this study [42]. There are four critical dimensions of distress covered in DDS, including emotional burden (Item 1, 4, 7, 10, 14), regimen distress (Item 6, 8, 3, 12, 16), interpersonal distress (Item 9, 13, 17), and physician distress (Item 2, 5, 11, 15).

#### 2.8.10. Cost-Effectiveness

Quality-adjusted life years (QALY) will be the main outcome parameter for the evaluation of cost-effectiveness from a societal perspective. EuroQol five-dimension Inventory (EQ-5D-5L) will be utilised in this study to calculate QALY. It is the most used instrument worldwide in economic evaluations that measure health benefits in terms of QALY [43]. English and Malay versions of EQ-5D-5L, which have been validated for use in the Malaysian population, will be utilised in this study [44,45].

EQ-5D-5L is a self-report questionnaire that assesses five life domains, including mobility, self-care, usual activities, pain/discomfort, and anxiety/depression [43]. There is also an EQ-VAS section to measure respondents’ perception of their overall current health on a vertical visual analogue scale with ‘100′ corresponding to ‘The best health you can imagine’ and ‘0′ representing ‘The worst health you can imagine’.

Scores on the five dimensions will be totalled up and converted into utility weights for computing QALY using the EQ-5D algorithm. Analysis will be conducted to estimate the direct and indirect costs for the intervention group and the control group for routine diabetes care. Intervention costs will then be estimated by using a bottom-up micro-costing analysis that will include meal replacement cost and operational costs such as dietician’s salary. The cost for control group or routine diabetes care will be estimated from a questionnaire on participant’s health care utilisation (general practitioner, dietician, physiotherapist, consultations at outpatient clinic, and hospitalisation) and use of medication.

The cost per QALY gained will be computed, and incremental cost-effectiveness ratios (ICER) will be calculated as the difference in costs divided by the difference in QALYs between the intervention and the control group using a bootstrap analysis. A cost-effectiveness plane can be plotted to indicate which intervention is more effective or expensive than the other.

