## 2. Methodology

### 2.1. Study Design

The study design is a two-armed randomised controlled clinical trial. Participants will be recruited into the study based on the inclusion and exclusion criteria (Table 1). Five thousand one hundred and eighty-five patients are screened through digital medical records in the database for their eligibility to be potentially recruited into the study.

Eligible and consenting participants will be randomised into two groups: (a) Meal replacement group (MR) and (b) Control group. The MR group will be receiving a meal replacement product and dietary consultation, while the control group will be receiving dietary consultation only. Outcome measurements will be assessed at the baseline, 6th week and after the completion of the 12-week intervention. Sociodemographic data, dietary information, and the quality of life of participants will also be recorded via questionnaires. Participants will also be monitored for 36 weeks after the completion of the meal replacement without any additional intervention. Another follow up will be done in week 48 and the same parameters will be measured. Hence, the total duration of the study is 48 weeks. A brief research flow chart is shown below in Figure 1.

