### 2.2. Sample Size

Sample size is calculated using G *Power 3.1 software. The protocol for calculation is as shown below in Table 2. We employed an effect size of 0.2055067, which is obtained from the mean difference value of the HbA1c (%) result in a study by Keogh and Clifton [18]. Based on the calculation, a total of 120 participants is needed for the study. In order to account for up to a 30% dropout, a total of 156 participants will be recruited for this study.

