### 2.4. Baseline Screening and Assessment

Subsequent to the recruitment, participants who have provided consent will be directed to the clinic for baseline assessment. Anthropometry and body composition measurements will be recorded. A research dietician will assess the dietary intake of the participants with a 3-day dietary recall and food frequency questionnaire on added sugar intake. Eighteen millilitres of blood will be collected by a qualified phlebotomist to measure HbA1c, fasting plasma glucose, fasting insulin, lipid, renal, liver profiles, and hormonal changes. Instruments to measure satiety, quality of life, and cost effectiveness will also be administered. A detailed list of baseline measurements is shown in Table 3, and the methods used for measurements are shown in the ‘data collection’ section.

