### 2.9. Statistical Analysis

Statistical Package for the Social Sciences (SPSS) program version 23.0 will be used to analyse the data. The data will be presented as mean ± SD for parametric data and median (range) for non-parametric data. The normality of data distribution will be tested using the Shapiro–Wilk test. A *p*-value of <0.05 will be used to denote statistical significance. Descriptive analysis including frequencies, percentage, mean, and standard deviation will be used to analyse sociodemographic data and blood pressure.

For the effects of meal replacement on metabolic profiles, anthropometric measurements, satiety levels, hormonal changes, and QoL scores, mixed-design ANOVA will be used to compare between the intervention group and the control group to determine the interaction effect of intervention and time.

To determine the cost-effectiveness, incremental cost-effectiveness ratios (ICER) will be calculated by dividing the difference in total costs (between control and treatment) with the difference in the chosen measure of health outcome or effect (QALY). To assess the sustainability of the meal replacement, mixed-design ANOVA will be used to compare clinical parameters and hormonal level changes between groups on week 12 and week 48.

The main analysis will be conducted in the intention-to-treat (ITT) population in which missing values will be predicted by using the estimating equation method by adapting statistical models to the data observed using the missing-at-random method. Complete case analysis will also be performed in the per-protocol (PP) population.

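### As described, the QALY difference in the ICER makes no use of the baseline EQ-5D-5L utility the trial collects, which costs precision and lets chance imbalance through

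*Protocol article*

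**What the plan says.** The estimator appears twice in the protocol article. Section 2.8.10 has the ICER "calculated as the difference in costs divided by the difference in QALYs between the intervention and the control group using a bootstrap analysis". Section 2.9 obtains it by "dividing the difference in total costs (between control and treatment) with the difference in the chosen measure of health outcome or effect (QALY"). Neither place mentions a covariate, a regression or the baseline utility. Neither calls the difference raw or unadjusted.

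Utility comes from one instrument: "EuroQol five-dimension Inventory (EQ-5D-5L) will be utilised in this study to calculate QALY" (2.8.10). It is available before randomisation. Section 2.4 says of the baseline visit that "Instruments to measure satiety, quality of life, and cost effectiveness will also be administered", and Table 3 marks EQ-5D-5L at weeks 0, 12, 24, 36 and 48.

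On balance between arms, section 2.5 says: "Gender (men, women), HbA1c (≤8.5% or >8.5%), and BMI (≤25 or >25) at the time of baseline measurement will be balanced in each group". Baseline utility is not among these factors. Section 1.1.2 lists cost-effectiveness as a secondary endpoint, and section 2.8.10 makes QALYs its main outcome.

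**The concern.** A QALY total accumulates utility over time and is not a change from baseline. If it is computed as the area under the utility curve, the week-0 value is part of the total. Each person's starting level also tends to persist into later visits. An arm that happens to start with higher utility will therefore show more QALYs whatever the meal replacement does.

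Nothing in the described method removes this. Utility is not a minimisation factor. The mixed-design ANOVA of section 2.9 compares the clinical and quality-of-life outcomes over time and does not produce the QALY difference. The bootstrap interval does reflect chance baseline variation in its width, but the bootstrap cloud is centred on the observed difference, imbalance included.

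At stake are the location and spread of the points on the cost-effectiveness plane. The QALY difference is the ICER's denominator, so when it is small a modest shift can matter to the ratio.

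**Working it through.** **The plan's own figure.** The article gives no precision figure for QALYs. Its only sample-size result is for HbA1c (Table 2), and it reproduces: λ = f²·N·m / (1 + (m − 1)ρ) = 0.2055067² × 120 × 4 / (1 + 3 × 0.5) = 8.1087, which gives power 0.8063 with 1 and 118 df. It is used here only for N = 120, that is 60 per arm at 1:1.

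**Inputs from the article.** EQ-5D-5L at weeks 0, 12, 24, 36 and 48 (Table 3); 48 weeks in total (2.1); 1:1 allocation (2.5).

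**Assumptions, none given in the article.**
- QALYs by the trapezoidal rule.
- The same utility SD, s, at each visit. SD 0.15 is used for illustration, with a range of 0.10 to 0.20.
- Correlation r from 0.3 to 0.7, in two structures: equal between all visits, or decaying as r to the power of the number of visits apart. Table 2's 0.5 is a planning value for HbA1c, not for utility.

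**Step 1, weights.** Each 12-week interval contributes 6/52 year to each of its ends. The weights are 0.1154, 0.2308, 0.2308, 0.2308, 0.1154, with sum 0.9231. Week 0 carries 0.1154 / 0.9231 = 12.5% of the total.

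**Step 2, effect of baseline imbalance.** The expected shift in the QALY difference per unit of baseline imbalance is b = Σ wⱼ·corr(u₀, uⱼ). With equal correlation of 0.5, b = 0.1154 + 0.5 × 0.8077 = 0.519.

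**Step 3, variance saved.** With R the correlation matrix, Var(QALY) = s²·w′Rw. Adjustment for u₀ removes the fraction b² / (w′Rw). With equal correlation of 0.5, w′Rw = 0.519, so the fraction is 0.519² / 0.519 = 0.519.

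| Structure | r | b | w′Rw | Variance cut | Shift per 0.01 imbalance |
|---|---|---|---|---|---|
| Equal | 0.3 | 0.358 | 0.386 | 33% | 0.0036 |
| Equal | 0.5 | 0.519 | 0.519 | 52% | 0.0052 |
| Equal | 0.7 | 0.681 | 0.652 | 71% | 0.0068 |
| Decaying | 0.3 | 0.213 | 0.305 | 15% | 0.0021 |
| Decaying | 0.5 | 0.325 | 0.414 | 25% | 0.0032 |
| Decaying | 0.7 | 0.497 | 0.557 | 44% | 0.0050 |

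**Step 4, how large a chance imbalance is.** The standard error of the baseline utility difference is s·√(2/60): 0.018, 0.027 and 0.037 for s = 0.10, 0.15 and 0.20. With s = 0.15 and r = 0.5, a one-standard-error imbalance of 0.027 moves the QALY difference as follows.
- Equal correlation: 0.519 × 0.0274 = 0.014. The unadjusted standard error is 0.15 × √0.519 × √(2/60) = 0.0197, which adjustment lowers to 0.0137.
- Decaying correlation: 0.325 × 0.0274 = 0.009. The unadjusted standard error is 0.0176, which adjustment lowers to 0.0152.

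**The case against.** The strongest objection is that the article does not commit to a raw difference. It gives the generic definition of an ICER and adds a bootstrap, and a baseline-adjusted difference would fit the same words. A condensed article may also leave covariates to an analysis plan or health-economic plan that is not shown. A reader might infer that the investigators have chosen to ignore baseline utility. The documents do not support that, because "raw" and "unadjusted" are not written. What stands is narrower. The article states this estimator in two places, the plain reading of both is a difference in arm means, and a team following the text would leave out a covariate already in hand.

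A reader might also infer that the result would be biased or invalid. It would not be. Randomisation makes the unadjusted difference unbiased on average, and the bootstrap interval allows for chance variation. The loss is precision, plus the imbalance realised in this particular trial.

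The size is open to challenge too. The trapezoidal rule is not stated, no utility SD or correlation is given, and equal correlation over 48 weeks is the favourable case. That objection is accepted, which is why the decaying structure is shown alongside.

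Finally, the gain could be presented as an increase in power. The article plans no significance test of QALYs and gives no QALY effect size, and the effect size in Table 2 belongs to HbA1c. No power claim is made.

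**Conclusion.** The point holds as an improvement to the described analysis, and not as a demonstration that the plan is wrong. As described in 2.8.10 and 2.9, the QALY difference leaves unused a baseline utility that is collected and is not balanced by design. Under the stated assumptions, adjustment removes 33% to 71% of the variance with equal correlation between visits, or about 15% to 44% with decaying correlation. Each 0.01 of baseline imbalance moves the unadjusted QALY difference by about 0.002 to 0.007.

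The direction does not depend on the exact assumptions as long as utility is positively correlated across visits; the size does. Whether the sign of the ICER would change cannot be said, because the article gives no expected QALY difference. The HbA1c and weight analyses are unaffected.

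**What to change.** State in 2.8.10, and in matching words in 2.9: *The incremental QALY will be the group coefficient from a linear regression of QALY on group, baseline EQ-5D-5L utility and the minimisation factors. The model will be re-fitted in each bootstrap resample together with the cost difference, and the ICER and cost-effectiveness plane will use the results. The unadjusted QALY difference will be reported as a sensitivity result.*

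Table 1 requires a BMI of at least 25, so the binary BMI factor split at 25 will be nearly constant. The text should say how BMI enters the model (for example as a continuous value) so that the fit does not fail in some resamples.

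The cost is a few sentences and one regression inside the bootstrap loop, with no new data, visits or participants. Section 3 reports that the intervention had not started, so the choice can still be fixed before follow-up utilities exist. If a separate analysis or health-economic plan already specifies the adjustment, bringing the two sections into line with it is enough.
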